##### PIP-UE

Presence of endometriosis (endometriosis or no endometriosis)Timing of endometrial injury (for example, during menstruation or not)Duration of infertility (for example, < 2 years, 2–5 years, >5 years)

For the outcome of pain during the procedure the following subgroup analysis will be performed:Previous cervical surgery (yes or no)Whether a tenaculum was used during the procedure (yes or no)Whether the procedure was performed during menstruation (yes or no).

Subgroup analyses will also be conducted to assess whether the probability of completing the endometrial biopsy procedure (that is, not abandoning the procedure) or needing a tenaculum to complete the procedure, is associated with the age of the woman or whether she had previous cervical surgery.

Any subgroup analyses conducted which are not pre-specified will be clearly stated as ad hoc and will be used for hypothesis generating only.

### Ethics and confidentiality

At the time of submitting this Protocol the PIP studies had received ethical approval from: 1) Northern A Health and Disability Ethics Committees, Ministry of Health, New Zealand, 2) Research and Human Research Ethics Committee, The Royal Women’s Hospital, Melbourne, Australia, 3) Research Ethics Committee, Faculty of Medicine, Cairo University, Egypt, 4) Ethics Committee of the Hospital of the Clinical Medical College, Riberio Preto, Brazil, 5) Institutional Ethics Committee, Queensland Fertility Group, Australia, 6) Regional ethical review board in Gothenburg, 7) Committee Medical Ethics, UZ KU Leuven/Research. All relevant ethics and locality approvals have been obtained prior to recruitment commencing at each participating site, and will be obtained prior to recruitment at any site that starts recruiting in the future.

All patient health information will be treated confidentially. Investigators and study staff will only have access to health information about participants recruited at their clinic; for example, site A will not have access to patient data from site B.

The PIP studies will be conducted according to the Principles of Good Clinical Practice as defined in the Medicines for Human Use (Clinical Trials) Amended Regulations 2006.

### Roles and responsibilities

The Chief Principal Investigator is [name], based at Fertility Plus, Auckland District Health Board, which is the coordinating site for the PIP studies. The coordinating centre is responsible for monitoring recruitment rates, communicating protocol changes to participants, investigators and clinical trial registries, and conducting data quality and completeness auditing. Together the Chief Investigator and at least one investigator from each recruiting site form the Steering Committee for the PIP studies. The role of this committee is to consider matters relating to protocol amendments and recruitment strategies. The results of the PIP studies will be published in peer-reviewed journals within 12 months of trial closure, and be uploaded to the trial registration website, as per WHO recommendations [49]. Authorship of any resulting publications will be governed by the Steering Committee. The results will also be made available to trial participants who indicated they wished to receive a trial report on their consent form.

The PIP trials are investigator initiated studies, and no study sponsor is applicable. Provisions relating to compensation for any adverse outcome associated with trial participation are organised on a case-by-case basis at the recruiting site.

### Participant withdrawal

Participants are free to withdraw from the study at any time. Prior to randomisation, participants will give their consent that any information collected about them, up to the point that they withdraw, can still be processed and analysed in the study. If a participant chooses to withdraw from the study, from this point onwards no further study procedures may occur and no further data may be collected. There is no replacement of participants who withdraw, as a contingency for this has been built into the sample size calculations.

### Protocol violations

Participants who do not follow the planned protocol are considered to have a protocol violation. This includes, for example, those for whom an endometrial biopsy is not successful or those who undergo an additional fertility treatment. The nature of the protocol violation will be documented for each participant. Participants who withdraw or who have a protocol violation will remain in the study denominator as per intention-to-treat principles.

### Interim analyses and data and safety monitoring

No interim analyses will be conducted. No data safety monitoring committee will be established.

Adverse events are defined as any untoward medical occurrence in a randomised patient regardless of its causal relationship to study treatment. Provision has been made for actively recording adverse events which are expected, for example, miscarriage, multiple gestations and pain during the procedure. Additionally, due to concern regarding the possible influence of endometrial disturbance on the implantation site of an embryo, the location of the placenta will be recorded following live birth.

Participants will be asked to report any other adverse events to the study coordinator when they occur; these will not be actively recorded. All adverse events that occur during the study period will be documented on a designated data form. It should be noted that endometrial biopsy is a safe and well-tolerated procedure which is routinely performed in women in whom uterine pathology is suspected, for example, women with menorrhagia. Adverse events and complications related to this procedure include infection, haemorrhage and perforation of the uterus, but these are rare [6, 7].

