### Outcomes

The primary outcome is live birth rate per woman randomised, as defined previously [35].

Secondary outcomes include:ongoing pregnancy per woman randomised (defined as continuing pregnancy diagnosed by ultrasonographic visualisation of one or more gestational sacs on or after 12 weeks gestation)clinical pregnancy per women randomised (defined as a pregnancy diagnosed by ultrasonographic visualisation of one or more gestational sacs, including ectopic pregnancy)biochemical pregnancy (defined as βhcg > 25 mIU/ml) PIP-IVF onlymultiple pregnancies per women randomised and per clinical pregnancy (defined as ultrasonographic visualisation of two or more gestational sacs or heartbeats)ectopic pregnancy per women randomised and per clinical pregnancy (defined as a pregnancy in which implantation takes place outside the uterine cavity)miscarriage per women randomised and per clinical pregnancy (defined as the spontaneous loss of a clinical pregnancy before 20 completed weeks of gestational age)neonatal characteristics (for example, gender, gestation at birth, malformations)placenta characteristics (placenta previa: major, placenta previa: minor, placental abruption, placenta accreta: previous uterine surgery, placenta accreta: no previous uterine surgery)pain during the procedure (as measured by a 10 cm visual analogue scale (VAS))bleeding the day following the procedure.

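### Placental recording is tied to live birth and no outcome names a loss from 20 weeks, so the placental safety comparison is open to selection, probably in very few women

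*Protocol article*

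**What the plan says.** Two sections of the protocol article bear on the point.

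**Interim analyses and data and safety monitoring.** The reason for collecting placental data is given as "due to concern regarding the possible influence of endometrial disturbance on the implantation site of an embryo", and the rule that follows is that "the location of the placenta will be recorded following live birth". No other time or trigger is given. Miscarriage, multiple gestation and procedural pain are given as examples of expected events that are actively recorded. Other adverse events rely on participants reporting them. There is no data safety monitoring committee and no interim analysis.

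**Outcomes.** The placental secondary outcome covers "placenta previa: major, placenta previa: minor, placental abruption, placenta accreta: previous uterine surgery, placenta accreta: no previous uterine surgery". It carries no live-birth condition and no denominator. Miscarriage is "the spontaneous loss of a clinical pregnancy before 20 completed weeks of gestational age". Ongoing pregnancy rests on "visualisation of one or more gestational sacs on or after 12 weeks gestation". No stillbirth, fetal death or other loss from 20 weeks is named, and the neonatal examples are sex, gestation at birth and malformations.

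**Tables 1 and 2** end in a birth column in which only live birth is marked. Adverse events are marked for the procedure visit and the day after, and in PIP-IVF for the intervention group only.

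**The concern.** The protocol singles out one biological harm and one measurement to check it. Abruption, praevia and accreta can themselves end a pregnancy. If placental findings are collected only when the baby is born alive, whether a woman is assessed depends on an event after randomisation that those conditions can prevent. Live birth is also the primary outcome, which the intervention is meant to change, so the women assessed in the two arms need not be comparable.

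At stake is the credibility of one safety comparison. With no monitoring committee, the end-of-trial tabulation is the main place where a placental signal would be seen. An analysis plan can choose denominators later, but it cannot supply findings that were never collected.

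**Working it through.** The protocol states no figure that this point depends on. The check is a comparison of sections, followed by arithmetic for scale.

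**1. Where a loss from 20 weeks would appear**

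| Item in the protocol | Captures a loss from 20 weeks? |
|---|---|
| Live birth (primary) | Yes, as a non-event, without a label |
| Clinical and ongoing pregnancy | Yes, as a pregnancy; the later loss is not shown |
| Miscarriage | No, capped at 20 completed weeks |
| Neonatal characteristics | Not named among the examples |
| Placental outcome (Outcomes section) | Not excluded, but no trigger given |
| Placental location (safety section) | No, recorded after live birth |
| Adverse events | Only if the woman reports it |

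The loss can be derived as ongoing pregnancy minus miscarriage minus live birth. The derivation is not clean: Statistical analysis imputes a missing live-birth outcome as no live birth, so late losses and women lost to follow-up look alike unless the missing data are flagged. Even a clean derivation gives only the count. The placental finding is not recovered.

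**2. Planned live births**

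Formula: (N/2) × (p1 + p2), with sample sizes and rates from Sample size.

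- PIP-IVF: 420 × 0.33 + 420 × 0.17 = 138.6 + 71.4 = 210
- PIP-UE: 175 × 0.20 + 175 × 0.07 = 35 + 12.25 = 47
- PIP-PCOS, assuming 12% and 5% per cycle compound over three cycles: 1 − 0.88³ = 0.319 and 1 − 0.95³ = 0.143; 140 × (0.319 + 0.143) = 65
- Total: about 322

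**3. Late losses**

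The protocol gives no rate. Let r be the assumed share of pregnancies reaching 20 weeks that are then lost. Losses = live births × r/(1 − r).

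| Assumed r | PIP-IVF | All three trials |
|---|---|---|
| 0.3% | 0.6 | 1.0 |
| 0.5% | 1.1 | 1.6 |
| 1% | 2.1 | 3.2 |
| 2% | 4.3 | 6.6 |

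Only some of these would be placental. If that share is assumed to be 10% to 30%, PIP-IVF would miss 0.6 × 0.10 = 0.06 to 4.3 × 0.30 = 1.3 cases.

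**4. What the selection does to a rate**

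Let q be the true rate of placental abnormality per pregnancy reaching 20 weeks, and f the share of affected pregnancies that are lost. Both are assumed, and other late losses are ignored. The rate seen among live births is q(1 − f)/(1 − qf).

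- q = 1%, f = 5%: 0.95%
- q = 1%, f = 20%: 0.80%
- q = 3%, f = 5%: 2.85%
- q = 3%, f = 20%: 2.41%

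The rate is understated by roughly the fraction f. If one arm had q = 3% and the other 1%, with f = 20% in both, the difference would shrink from 2.00 to 2.41 − 0.80 = 1.61 percentage points. The ratio would stay close to 3 (2.41/0.80 = 3.01). The ratio is materially distorted only if the share lost also differs between arms.

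**The case against.** The strongest case against the point has four parts.

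- **The restriction is partly inferred.** The safety section gives one time point for placental location and does not say that nothing is recorded otherwise. The Outcomes section lists a wider set of characteristics with no live-birth condition. This stands: the two sections are unreconciled, and a full form might capture more. But no other trigger appears anywhere, and the one stated rule is a data-collection rule, so more than ordinary condensation is involved.
- **Other routes exist.** An adverse event is defined broadly enough to include a stillbirth or an abruption, and participants are asked to report such events. This stands too, but the capture is passive. The defined on-study periods end well before 20 weeks, and the protocol does not say whether its adverse-event period runs longer. Active recording of miscarriage suggests that it may.
- **The missing denominator proves little.** Biochemical pregnancy and neonatal characteristics have none either. This is right. The silence does not show that the placental outcome will be analysed per live birth.
- **The comparison is weak under any form design.** With eight placental cases in PIP-IVF, a 7 v 1 split in 420 per arm gives Fisher p = 0.07; two cases split 2 v 0 give p = 0.50. This stands, and it limits what the fix can achieve.

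A reader might infer that the gravest implantation-site harms are all selected out, that late losses are invisible, or that the comparison is biased towards safety. The documents do not support these readings. Ectopic pregnancy and losses before 20 weeks are counted per woman randomised and per clinical pregnancy. A late loss counts as a clinical pregnancy and, if scanned as planned, as an ongoing one. Bias towards safety requires that a harm exists and, on the ratio scale, that affected pregnancies are lost more often in the biopsy arm.

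**Conclusion.** The point holds in a limited form. Following the stated rule, a pregnancy lost from 20 weeks has no planned placental record and no named outcome, so the placental comparison is open to selection on a post-randomisation event. The mismatch between the Outcomes section and the safety section follows from the text and needs no assumption.

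The size does rest on assumptions. At a late-loss rate of 0.3% to 2%, about 1 to 4 losses would be expected in PIP-IVF and about 1 to 7 across the three trials, with probably a handful of placental cases at most. The live-birth counts behind this use the protocol's planning rates. Because so few placental events are expected at all, one missing case would be visible in the table, but it would seldom change a formal comparison.

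The primary analysis is unaffected: a late loss is correctly counted as no live birth per woman randomised. This is a minor to moderate improvement in safety reporting.

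**What to change.** - In the safety section, replace the live-birth trigger so that placental characteristics are recorded for every pregnancy reaching 20 weeks, whatever its outcome. Use the same item list as the Outcomes section, so that the two agree on what is recorded and for whom.
- Add pregnancy loss from 20 weeks (stillbirth) to the secondary outcomes as a safety outcome. This closes the gap above the miscarriage limit and separates true late losses from imputed missing outcomes.
- Report both per woman randomised, which preserves the randomised comparison, and also per ongoing pregnancy as a descriptive figure.

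The Follow-up section already obtains live birth from participants, hospital records or centre outcome data, and the same sources can serve here. The cost is a changed form trigger, one added outcome line and a few more hospital records to retrieve. No extra procedure, visit or participant is needed.

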### Eligibility assessment

Potentially eligible women will be informed about the PIP study by invitation letter, advertisement (for example, poster or newsletter) or their treating clinician or nurse. All potential participants will have the opportunity to ask questions about the study and discuss any concerns or queries prior to making a decision about whether to take part. Informed consent will be obtained from all participants in writing prior to their recruitment. Informed consent will be undertaken by a PIP study researcher who is familiar with the study details and has adequate training and experience in trial recruitment (see Tables 1 and 2).

**Table 1 Tab1:** Schedule of procedures and outcome measurements for PIP-IVF

	Pre-study	Day 1 of prior cycle	Day 3 of prior cycle-day 3 of IVF/embryo transfer cycle	Day after procedure	IVF cycle/embryo transfer	About 2 weeks after embryo transfer	About 6 weeks gestation	≥12 weeks gestation	Birth
Eligibility screen	x								
Informed consent	x								
Randomisation		x							
Endometrial scratching (intervention group only)			x						
Pain (VAS) (intervention group only)			x						
Adverse events (intervention group only)			x	x					
Bleeding (intervention group only)				x					
IVF cycle characteristics					x				
Biochemical pregnancy						x			
Clinical pregnancy							x		
Ongoing pregnancy								x	
Live birth									x

**Table 2 Tab2:** Schedule of procedures and outcome measurements for PIP-UE and PIP-PCOS

	Pre-study	Day 1-12 of cycle 1	Day after procedure day	End of study/end of cycle 3	About 6 weeks gestation	≥12 weeks gestation	Birth
Eligibility screen	x						
Informed consent	x						
Randomisation		x					
Study intervention		x					
Pain (VAS)		x					
Adverse events		x	x				
Bleeding			x				
Cycle characteristics (e.g., intercourse frequency, ovulation medication dose (PIP-PCOS only), via study diary)				x			
Clinical pregnancy					x		
Ongoing pregnancy						x	
Live birth							x

The details of all women assessed for eligibility will be recorded to ensure reporting as per the CONSORT statement [40]. This record will include reasons for ineligibility or nonparticipation.

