#### Placebo procedure

In PIP-PCOS and PIP-UE, women in the control arm of the trial will undergo a placebo procedure which is designed to blind participants to their allocation. If couples who are attempting to conceive with sexual intercourse are aware of their study allocation, they may purposely or inadvertently influence their pregnancy outcome through behavioural changes, such as a change in sexual frequency or timing.

For the placebo procedure the women will lie in the dorsal or lithotomy position and a speculum will be inserted into the vagina. The biopsy catheter will be placed at the posterior fornix but not inserted into the external os of the cervix. The internal piston is withdrawn and the catheter moved and rotated slightly to replicate the standard biopsy action. The catheter is then removed, followed by the speculum. The catheter is then discarded.

Participants randomised to the control group in PIP-IVF will not undergo any procedure that is additional to standard care.

Shortly following the procedure and before leaving the clinic, participants will be asked to record the pain they experienced during the procedure on a 10 cm VAS. Participants will also be handed an information leaflet detailing what to expect following an endometrial biopsy, and told to seek medical attention and contact the study coordinator if they experience any adverse events that are potentially associated with the procedure, for example, heavy bleeding or signs of infection such as foul smelling discharge.

In PIP-IVF, participants will be contacted within one week of the procedure and asked to report whether they had any vaginal bleeding the day following the procedure. Women in PIP-PCOS and PIP-UE will be asked to complete a study diary for the three study cycles. In this diary they will record the date of the procedure, whether they had any vaginal bleeding the day following the procedure, each day that they have their period and each time they have sexual intercourse during the on-study period. Women will continue to complete the study diary until their third period following the procedure or until confirmation of a clinical pregnancy (that is, all patients have three cycles or opportunities for conception within the on-study period). Participants should be contacted at least once a month to check in and ensure they are completing the study diary and to provide an opportunity to identify any protocol violations.

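### PIP-UE and PIP-PCOS state no enquiry about infection or heavy bleeding after the day following the procedure, so late cases may be under-counted (minor)

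*Protocol article*

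**What the plan says.** The point concerns the two sham-controlled trials. PIP-IVF is left aside, because its Table 1 collects adverse events in the intervention group only and no monthly contact is described for it.

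- **Schedule.** Table 2 (Eligibility assessment), titled "Schedule of procedures and outcome measurements for PIP-UE and PIP-PCOS", marks the adverse-event row in two columns: the procedure visit in cycle 1 and the day after. The columns for end of cycle 3, six weeks, 12 weeks and birth are blank in that row.
- **Active recording.** Interim analyses and data and safety monitoring states: "Provision has been made for actively recording adverse events which are expected, for example, miscarriage, multiple gestations and pain during the procedure".
- **Other events.** The same section continues: "Participants will be asked to report any other adverse events to the study coordinator when they occur; these will not be actively recorded". It then adds: "All adverse events that occur during the study period will be documented on a designated data form".
- **Known complications.** That section also says: "Adverse events and complications related to this procedure include infection, haemorrhage and perforation of the uterus, but these are rare".
- **Prompt.** Under Placebo procedure, women are given a leaflet before leaving the clinic and "told to seek medical attention and contact the study coordinator if they experience any adverse events that are potentially associated with the procedure", with the illustration "for example, heavy bleeding or signs of infection such as foul smelling discharge".
- **Later contacts.** The same section says: "Participants should be contacted at least once a month to check in and ensure they are completing the study diary". Finding protocol violations is the other stated purpose. The diary has one bleeding item tied to the procedure, for the following day; after that it logs period days and intercourse.

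**The concern.** Infection or heavy bleeding after a biopsy can begin later than the next day. For that interval the article states no question about either, although it names infection and haemorrhage as complications of the procedure. A woman treated by her own doctor may never tell the study coordinator.

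These two trials have a sham arm followed on the same schedule, so they are well placed to count late complications of a biopsy done in a cycle in which the woman is trying to conceive. A low or zero count resting mainly on self-report is weaker evidence of safety than the same count after a direct question. The article also plans no interim analysis and no data safety monitoring committee, so what individual women report matters more.

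The stakes are limited. The primary outcome does not depend on this, and infection is not among the listed outcomes.

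**Working it through.** The article gives no late-event rate and no reporting share, so there is no figure of its own to reproduce.

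**1. The texts side by side.** The data-form sentence governs what is written down once an event is known; it adds no question. The prompt to women is real and names the right events, but it relies on their initiative. The monthly contact has stated purposes, and adverse events are not among them. The allocation guess (Assessment of participant blinding) takes place within one week for the early-ask group and at study end for everyone; it asks about allocation. Data collection says some information comes from patient notes, without saying that the notes are searched for adverse events. Documentation therefore continues throughout the study, but no enquiry about these complications is stated after the day following the procedure.

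**2. Is the monthly contact early enough?** The earliest exit is a clinical pregnancy in cycle 1, seen on ultrasound at about six weeks gestation (Follow-up). Assume gestation is counted from day 1 of the procedure cycle. Six weeks is then cycle day 43. With the procedure on day d, from 1 to 12, the interval to the scan is 43 − d:
- d = 1: 42 days
- d = 12: 31 days

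On that assumption, a first contact within about 30 days comes before even the earliest exit.

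**3. What full capture could show.** Planned totals are 350 (PIP-UE) and 280 (PIP-PCOS), allocated 1:1, so 350/2 = 175 and 280/2 = 140 per arm. With zero events, the upper one-sided 95% bound is 1 − 0.05^(1/n):
- n = 175: 1.70%
- n = 140: 2.12%

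**4. Illustration of under-capture.** Let r be the true late-event risk and s the share captured; both are assumptions. The chance of recording at least one event in an arm is 1 − (1 − r·s)^n.

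| n | r | s = 100% | s = 50% |
|---|---|---|---|
| 175 | 0.5% | 58.4% | 35.5% |
| 175 | 2% | 97.1% | 82.8% |
| 140 | 0.5% | 50.4% | 29.6% |
| 140 | 2% | 94.1% | 75.5% |

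**5. Comparison of arms.** Assume true risks of 2.0% (biopsy) and 0.5% (sham).
- Equal capture of 50%: the risk ratio stays at 1.0%/0.25% = 4, and the difference falls from 1.5 to 0.75 percentage points.
- Unequal capture: the ratio moves. With 75% captured after biopsy and 50% after sham it is 1.5%/0.25% = 6. With the shares reversed it is 1.0%/0.375% = 2.7.

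**The case against.** The strongest reply is that this is an openly stated, pragmatic choice and that the missing detail may sit in the call script or data form, which a journal article omits. The list of actively recorded events is open-ended, and infection and haemorrhage, being known complications, could belong to the expected class. Blank cells in Table 2 are weak proof: miscarriage is actively recorded, yet it has no row of its own and no later adverse-event mark. The diary logs period days across three cycles, and several later contacts exist at which an event could come up. The complications are described as rare, and an amendment to ongoing trials has a cost.

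Much of this stands as a limit on the wording. A reader might infer that late infection and heavy bleeding are captured by self-report and by nothing else. The documents do not go that far, because the list is open and the diary and contacts may bring some cases to light. A reader might also infer that adverse events go undocumented after the next day; the data-form sentence rules that out.

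The reply does not remove the point. Passive reporting of the remaining events is a stated rule, not just an omitted detail. The contact best placed to ask has stated purposes that do not include adverse events. The diary records period days but not how heavy the bleeding was, and it has no stated item on infection.

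**Conclusion.** The concern holds as a minor point of safety ascertainment. No enquiry about procedure-related infection or heavy bleeding is stated after the day following the procedure in PIP-UE and PIP-PCOS. Late cases appear to depend mainly on prompted self-report and may be under-counted.

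The size of the shortfall cannot be derived from the article. The figures in steps 4 and 5 rest on assumed risks and capture shares, and the timing in step 2 on an assumed gestation count. The zero-event bounds of 1.7% and 2.1% show that the gain is modest: a more reliable count by arm, not a test.

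It is tempting to add that any loss is the same in both arms and so cannot distort the comparison. That is true of the schedule only. Assessment of participant blinding concedes that the sham is expected to hurt less and that blinding may suffer, and Blinding says the operator knows the allocation. Reporting could therefore differ by arm, although nothing in the article shows that it does.

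**What to change.** - **Question.** At the first monthly contact after the procedure, in both arms of PIP-UE and PIP-PCOS, ask one fixed question: since the procedure, has the woman had fever or foul smelling discharge, heavy bleeding, or needed medical attention or antibiotics?
- **Text.** Amend Interim analyses and data and safety monitoring to say that infection, heavy bleeding and treatment for either are asked about at that contact, while other unexpected events remain self-reported. Add the contact to the adverse-event row of Table 2.
- **Reporting.** Give counts and percentages by arm for each trial, and state how many women were enrolled before the change. No significance test is needed.

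**Cost.** No extra visits, staff or procedures are needed. Calls become slightly longer and more minor events will need documenting. Recruitment began in June 2014, so this is a small amendment to ongoing trials, through the Steering Committee and the seven ethics bodies listed, as each requires. Ascertainment will differ between women enrolled before and after the change.
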